## Analysis

### Power calculation

In this retrospective study, the sample size is fixed. The Evaluability Assessment estimated around 3000 births in FNP cohorts between 2010 and 2015 and around 6000 in the Controls [24]. This large sample size would permit very precise estimation of overall intervention effects for a primary or co-primary outcomes. However as specified by Scottish Government, there is no pre-specified prioritisation of the short- or medium-term outcomes and as such no power calculation is necessary. 

### Identification of Cases and Controls

#### Cases

The number of Cases identified and received from FNP SIS and matched to the SMR02 dataset by eDRIS will be reported. Additional checks will be made on the eligibility of FNP clients using SMR02 fields (age at enrolment vs age at booking, age at Last Menstrual Period gestational age at enrolment vs. booking). This will allow us to measure the robustness of these fields used to identify the Controls.

#### Controls

In a natural experiment, to enable an unbiased comparison of Cases and Controls, measured risk factors associated with outcomes (known as covariates) should be sufficiently similar (and thus balanced) for both exposure groups. As the potential Controls would have been eligible for enrolment on FNP during a period of non-recruitment, they are already a more homogenous comparison population (according to age, area and parity). It is likely, therefore, that the Controls will be sufficiently similar to Cases. However, a possible threat to an unbiased comparison is the enrolment of mothers into FNP on criteria other than age, area and parity, and balance may not be adequate. For example, if mothers who are approached but not enrolled in FNP differ from those who are enrolled for characteristics that are associated with variation in outcomes, comparisons with all eligible Controls may under- or overestimate any effect of FNP. One way to address this is to match the population further as it may provide a more valid estimate of effects because only women with similar observed characteristics are included. The disadvantages of this approach would be that not all Cases would be matched to Controls, which would risk the exclusion of Cases and reduce the sample size. The approach taken here will retain all Controls and given the possibility of a homogeneous comparison group, results will be more generalizable, and result in higher power.

### Descriptive analysis: Cases and Controls

Measurable pre-recruitment/at booking maternal demographics and socioeconomic covariates associated with the FNP enrolment and outcomes were decided a priori (Table 4). Covariates should be those that are not affected by exposure and measured before recruitment into FNP. The maternal characteristics will be described in Cases and all Controls using summary statistics (e.g. N (%), mean (standard deviation (SD))).

**Table 3: Maternal baseline characteristics measured at (or before) date of antenatal booking/enrolment table-3:** SMR: Scottish Morbidity Record; FNP SIS – Family Nurse Partnership Scottish Information System;

Dataset	Variable
SMR02	Health Board based on postcode at antenatal booking date
SMR02	Scottish Index of Multiple Deprivation (SIMD) quintile
SMR02	Ethnic Group (White/Other)
SMR02	Age at antenatal booking (years)
SMR02/FNP SIS	Age at last menstrual period (LMP) (years)
SMR02/FNP SIS	Completed weeks of gestation at antenatal booking/FNP enrolment date
SMR02	Maternal Height/Weight/Body Mass Index at booking date
SMR02	Booking Smoking History (never/non-smoker/current/former)
SMR02	Smoker during pregnancy recorded at booking (never/non-smoker/former/current)
SMR02	Drug misuse during pregnancy recorded at booking (yes/no)
SMR02	Illegal drugs/inappropriate injection of prescribed drugs at booking (yes/no)
SMR02	Typical weekly alcohol consumption at booking (units)
SMR02	Diabetes (pre-existing, gestational, yes but time of diagnosis unknown/no diabetes during this pregnancy, not known)
Dispensing	Drugs ever dispensed for asthma (yes/no)
Dispensing	Drugs ever dispensed for mental ill health (yes/no)
SMR02	Previous pregnancy (yes/no)
SMR02	Outcome of pregnancy (live/stillbirth/termination)
Child protection register	Ever been on child protection register
Looked after children	Ever looked after child
School/Pupil Census	Ever had a Free School Meal
School/Pupil Census	Ever had a student need
Attendances, Absences and Exclusions	Ever been excluded
Attendances, Absences and Exclusions	Attendance rate
Mother left school or still in school at booking date	School leavers (Summer and Christmas)

### Main analyses

With no primary outcome, equal importance will be given to each short and medium term outcome. All comparative analyses will therefore be exploratory, pre-specified and conducted on an intention to treat (ITT) basis. ITT in this study means that the analysis will include everyone who started the programme, according to their original ‘allocation’, i.e. the intervention group will be women enrolled in FNP regardless of the treatment (intervention) they actually received.

All analyses will compare outcomes (intervention effect) between the two groups (Cases and Controls) using multilevel regression models, to allow for clustering of outcome within NHS HB, and FNP team/cohort (where more than one team runs within a HB). Multiple births will be analysed as separate children and the potential clustering of outcome will not be taken account for in analyses due to the small numbers expected. Intervention effects will also be examined over time and between different geographical areas (HB and team/cohort) by fitting multilevel models and interactions (group x year). Alongside the estimate of effect, for all outcomes a 95% confidence interval (CI) and unadjusted p-value will be presented.

Binary outcomes will be modelled using a logistic model and presented as odds ratios comparing the odds of an event in a case compared with the Control. For continuous outcomes a multilevel linear model will be fitted and results presented as a difference in means (Case minus Control group). Time to event analyses (e.g. cessation of breastfeeding, time to subsequent birth) will be analysed using a proportional hazards regression model and results presented as hazard ratios. We will ascertain if the proportional hazards assumption has not been violated by inspecting the log (-log(survival)) plot and Schoenfeld residuals. Count data will be analysed using a Poisson multilevel model. If the distribution of events display signs of over dispersion (greater variance than might be expected in a Poisson distribution), then a Negative Binomial model will be used. Results will be presented as the incidence rate ratio in the case arm compared to the Control group. The impact of FNP visits (dosage of intervention) on outcomes will be explored as a sensitivity analysis. Adherence will be defined as the number of FNP visits that a Client received during their programme enrolment overall or by phase (pregnancy, infancy, toddler), dependant on outcome. A number of other sensitivity analyses are proposed including adjustment for any imbalance in confounders (pre-exposure maternal and baby characteristics) (note that these will be assessed for the differing denominators (study populations) dependent on outcome) and adjustment for multiple testing.

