**Methods:**

This study is a natural experiment with a case-cohort design using linked anonymised routine health, educational and social care data. Cases will be women enrolled as FNP Clients in ten NHS Health Boards in Scotland and Controls will be women who met FNP eligibility criteria but were pregnant at a time when the programme was not recruiting. Outcomes are mapped to the Scottish FNP logic model. All comparative analyses will be pre-specified, conducted on an intention to treat basis and will use multilevel regression models to compare outcomes between groups.

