### Identifying Cases and Controls

#### Cases

Cases will be women and first-borns enrolled as FNP Clients in the ten participating Scottish Health Boards (HB) since its initiation from 1st January 2010 to 31st March 2016. Eligible women (criteria in Table 1A) are usually referred to the local FNP team after their antenatal booking appointment at around 12 weeks gestation and are required to be enrolled in the programme before 29 weeks. Cases will be identified from the FNP Scottish Information System (FNP SIS).

**Table 1: Maternal baseline characteristics measured at (or before) date of antenatal booking/enrolment table-1:** ^1^Either Health Board level or smaller geographical area such as Community Health Partnership level or where a recruitment area was defined by travel time ^2^Derived by Electronic Data Research and Innovation Service (eDRIS) SMR: Scottish Morbidity Record

A. FNP Clients eligibility criteria	B. Eligibility criteria applied to fields within SMR 02 dataset to identify Controls
1. Living in an FNP-recruiting NHS Health Board	Postcode at antenatal booking mapped onto each FNP recruiting area1
2. First time mothers-to-be (women are eligible if a previous pregnancy resulted in a miscarriage, stillbirth or termination)	No previous live birth
3. Aged 19 years or younger at time of last menstrual period (LMP)	Derived variable2 based on date of birth and date of LMP
4. Less than 28+6 weeks gestation at enrolment into FNP	Gestation at booking date (derived variable2 based on date of booking and date of LMP)

Exclusion criteria

5. Mother-to-be will relinquish baby at birth	Not measurable at recruitment – minimal risk to numbers
6. Moving outside of the FNP catchment area before programme end	Not measurable at recruitment – minimal risk

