#### Controls

The FNP eligibility criteria in Table 1A will be applied to fields in the Scottish Morbidity Record (SMR) 02 Maternity Inpatients and Day Cases dataset to identify potential Controls for each of the areas within the ten participating HBs. Controls’ antenatal booking date will be taken as a proxy for FNP enrolment date (index date). Controls will be women that would have been potentially eligible for FNP, but whose antenatal booking occurred during a period when local FNP teams were not enrolling women. Alongside the eligibility criteria, using the start and end dates of FNP enrolment (including any intervals when cohorts ceased enrolment) provided to us by the FNP SIS, eDRIS will identify individual Controls with antenatal booking dates:

i. in the 12 months prior to initiation of FNP enrolment (Pre-FNP);

ii. in the 12 months post FNP enrolment (Post-FNP);

iii. between periods of FNP enrolment (i.e. when enrolment was temporarily suspended due to caseload capacity, usually up to a maximum concurrent caseload of 25 women, being reached) (Interval).

Further ineligibility criteria are applied to women during the FNP enrolment process, such as planning to place the child for adoption or moving out of the area, but cannot be applied in the selection of Controls as they are not assessed in the SMR02 (or any other dataset) at date of booking.

Within the enrolment period, a second cohort of women exist consisting of women eligible for enrolment into the programme during a period of active FNP enrolment and who:

iv. were approached for FNP but not enrolled to the programme;

v. were not approached (e.g. insufficient capacity in team to offer to all eligible women; near end of enrolment period and caseloads nearly full).

Following advice from the Public Benefit and Privacy Panel (PBPP), it was not possible to access individual level data for these women (in iv and v). However, it is important to note that these groups may have different demographic, social or personal characteristics from those that enrolled in the programme and may differ non-randomly from the Cases for some variables. As it would be beneficial to the evaluation to understand the characteristics of (iv) and (v) above and understand if they differ from Cases and Controls in anyway, aggregate statistics will be provided by eDRIS to the study team. 

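### Case/Control status is set by enrolment period within area, but no stated clustering level captures period-to-period variation for both groups, so confidence intervals can be too narrow

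*Protocol article*

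**What the plan says.** Main analyses names the clustering levels for all comparative models: multilevel regression "to allow for clustering of outcome within NHS HB, and FNP team/cohort (where more than one team runs within a HB". The second level is thus restricted to Boards with more than one team. Calendar time appears separately, as a group-by-year interaction used to examine whether effects change over time; it is not described as a clustering level.

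The Controls section sets exposure by place and time. The eligibility criteria are applied "to identify potential Controls for each of the areas within the ten participating HBs", and Controls are women "whose antenatal booking occurred during a period when local FNP teams were not enrolling women". They come from the 12 months before enrolment began, the 12 months after it, and gaps "between periods of FNP enrolment (i.e. when enrolment was temporarily suspended due to caseload capacity". Eligible women who booked while a team was enrolling but did not join are not available as individual records.

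Table 1 gives the area criterion for Controls as "Postcode at antenatal booking mapped onto each FNP recruiting area", and its footnote allows areas smaller than a Board.

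**The concern.** In the analysed data, group membership is essentially constant within an area and period: enrolment periods hold Cases and the other periods hold Controls. The comparison is therefore between periods within areas. Whatever the women of one area and period share besides the programme (local maternity services, recording practice, local events) adds to the variance of the group effect, and more women per period do not remove it.

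The stated levels do not carry this variation for both groups under either reading of team/cohort:

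- **Read as team area**, the level can be assigned to everyone, but it pools the Case and Control periods of that area.
- **Read as enrolment cohort**, it separates periods for Cases only. A cohort consists of enrolled women, and the article does not say what value a Control takes.

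In a single-team Board neither version is fitted, so successive cohorts and gaps share one Board intercept.

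At stake is the calibration of the intervals and p-values reported for the short- and medium-term outcomes, which are meant to inform policy.

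**Working it through.** The article states no ICC, design effect or power on this point, so it has no figure to reproduce.

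**Inputs from the article**
- Ten Boards (Abstract, Methods: "Cases will be women enrolled as FNP Clients in ten NHS Health Boards in Scotland").
- Sample size (Power calculation): "around 3000 births in FNP cohorts between 2010 and 2015 and around 6000 in the Controls".
- Each outcome gets a 95% interval and an unadjusted p-value (Main analyses).

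**Assumed, because not given**
- Five periods per area: pre, cohort 1, interval, cohort 2, post. That is two Case and three Control periods.
- J = 10 or 20 areas, with equal cells.
- Area-period ICC from 0 to 0.02, on an outcome scaled to unit variance.

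**Formulae**
- Variance of the group difference with no area-period term: V0 = 1/3000 + 1/6000 = 0.0005.
- True variance: V = (1 − ICC) × 0.0005 + ICC × [1/(2J) + 1/(3J)]. The bracket is 0.08333 for J = 10 and 0.04167 for J = 20.
- SE ratio r = √(V/V0). Actual coverage of the nominal 95% interval = 2Φ(1.96/r) − 1.

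**Worked example, J = 10, ICC 0.005**
- V = 0.995 × 0.0005 + 0.005 × 0.08333 = 0.0004975 + 0.0004167 = 0.000914.
- V/V0 = 1.83, so r = 1.35.
- Coverage = 2Φ(1.45) − 1 = 85.3%.

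| ICC | SE ratio, 10 areas | Coverage, 10 areas | SE ratio, 20 areas | Coverage, 20 areas |
|---|---|---|---|---|
| 0 | 1.00 | 95.0% | 1.00 | 95.0% |
| 0.001 | 1.08 | 93.1% | 1.04 | 94.0% |
| 0.005 | 1.35 | 85.3% | 1.19 | 90.1% |
| 0.01 | 1.63 | 77.1% | 1.35 | 85.3% |
| 0.02 | 2.08 | 65.5% | 1.63 | 77.2% |

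**Simulation check (10 areas, 3,000 runs per ICC).** For the same five ICC values, coverage without the area-period term was 94.6%, 93.3%, 84.7%, 76.4% and 65.5%. An analysis of period means with Board effects (50 cells − 11 parameters = 39 degrees of freedom) covered between 94.0% and 95.3% over ICC 0 to 0.02.

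**A cohort term for Cases only.** The model variance becomes (1 − ICC) × 0.0005 + ICC/(2J). With 10 areas, coverage is 94.3% (ICC 0.001), 92.4% (0.005), 91.0% (0.01) and 89.7% (0.02). The shortfall is smaller but remains.

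**Sensitivity to layout.** With three periods per Board (one Case, two Control) and 10 Boards, the bracket is 1/10 + 1/20 = 0.15. At ICC 0.005 the variance ratio is (0.0004975 + 0.00075)/0.0005 = 2.50. The five-period layout gives 1.83 with 10 areas and 1.41 with 20.

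**The case against.** Several stronger readings are tempting, and the article does not support them.

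- **That the second level does not exist for Controls.** Main analyses itself treats team/cohort as a geographical unit, and Table 1 maps each Control's postcode to a recruiting area. A team area is definable for every Control. Only the cohort or period part is undefined.
- **That dropping the level in single-team Boards is in itself an error.** There, team and Board largely coincide, so a separate team effect would add little. The loss is the period part.
- **That standard errors are understated in all 34 models.** This would need period variation in every outcome, and no ICC is given. At ICC 0 there is no shortfall, and at 0.001 it is small. A cohort term for Cases is a recognised partially nested model and would recover part of the loss where fitted.
- **That the remark "This large sample size would permit very precise estimation of overall intervention effects" is contradicted.** In context it concerns hypothetical primary or co-primary outcomes, and the article then declines to prioritise any. It is not a precision claim for these models.

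Two further points have weight. The group-by-year term could absorb calendar trends common to all areas if year is in the model, though not shocks specific to one area. Also, a detailed analysis plan is to be written before data access, and the coding of Controls and the choice of degrees of freedom could properly sit there. What remains is that the article does fix the levels, including the restriction to multi-team Boards, and as fixed they omit the unit at which exposure varies.

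**Conclusion.** The point holds conditionally. The stated levels contain no area-by-period term for both groups, although exposure varies at that level. If outcomes vary between periods within an area, the intervals for the group effect will be too narrow.

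On the assumed five-period layout the effect is nil at ICC 0, small at 0.001 and material from about 0.005. These figures describe a model with no area-period term at all. Variation between Boards or areas alone does not cause the problem, because Cases and Controls are compared within the same areas. The ICC, the number of areas and the number of periods are all assumptions. The direction is the same in each layout tried; the size is not.

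**What to change.** Define the second level as FNP recruiting area by enrolment period (pre, cohort k, interval k, post) for every woman in every Board. Assign it from booking postcode together with enrolment date for Cases and booking date for Controls.

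Include it alongside Health Board in all comparative models, as a random effect, as shared frailty in the hazard models, or through cluster-robust standard errors at that level. Add a small-sample correction suited to the model. Kenward-Roger serves the linear models only; for the logistic, count and hazard models, use t-based inference on the number of area-period cells. Whether Board enters as fixed or random is a matter of preference.

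The cost is low. Postcode, booking date and the enrolment start and end dates are already used to select Controls, and the analysis plan is to be written before data access. The price is somewhat wider intervals, with little lost if the area-period variance proves close to zero.

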#### Health Boards (HB)

Each HB in Scotland acts as the Data Controller for the data held on the FNP Scottish Information System (FNP SIS), a national database of FNP data accessible to Family Nurse (FN) teams. Agreement has been sought to allow these data to be processed by eDRIS for this study. Data include both identifiable data that will enable linkage to FNP Clients’ routine data from health, education and social care as well as clinical data recorded by FNs during their visits.

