CHSP-Pre-School- Health Visitor first visit (~10 days); 6-8 week review; 27-30 month review; unscheduled review	Contains data on the findings and outcome of the child health reviews for all children in Scotland. Child health reviews incorporate assessment of children's health, development, and wider wellbeing alongside provision of health promotion advice and parenting support.	NHS NSS	✓
CHSP-School - Primary 1 - screening and assessment	A Primary 1 review is offered to all children in Scotland in mainstream and special state schools at the age of 5 as part of the wider child health programme. It contains information on include height and weight measurements, and recording of diagnoses/concerns. Following the primary 1 screening some children have a further assessment which reviews the child's development (e.g. gross motor, fine motor, speech and language, social skills and behaviour).	NHS NSS	✓
FNP Scottish Information System	Contains information on the FNP programme delivery from enrolment in the programme.	Local HBs	✓
School/Pupil Census	Contains information on early learning and childcare provision, pupils, teachers, and school buildings collected from all Local Authority and Grant-aided schools and school centres on publicly funded schools.	SG		✓
Attendance, Absence and Exclusions	Contains information from schools on pupils attendance and absence from schools and the reasons for this. It also includes exclusions.	SG		✓
School Leavers (Summer and Christmas)	Contains information on pupils in each school year who leave school having attained the minimum school leaving age.	SG		✓
Skills Development Scotland: destinations	Contains data on 16-19 year olds in Scotland on school leaver destinations and type of destination (higher education, further education, employment, training, unemployed).	SG		✓
Children and Young People: Looked after children	Each Scottish Local Authority is asked to submit a return providing information on the Looked After Children for which they are responsible.	SG		✓
Children and Young People: Child protection register	Child protection data via the from Local Authorities’ Management Information Systems. The information collected here is the primary national data source on child protection in Scotland.	SG		✓
Scottish Credit and Qualifications Framework	Contains information on the qualifications awarded to learners in Scotland.	SG		✓

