Achievement of Curriculum for Excellence levels collections	Achievement of Curriculum for Excellence for all pupils in the stages of Primary (P)1, P4, P7, and Secondary (S)3, who are based on the roll of the school, and for all pupils based in standalone school/units. Each of the following will be collected: Numeracy, Reading, Writing and Listening and Talking.	SG		✓

The specification for this evaluation of FNP requires there be no pre-specified primary outcome(s). The outcomes of this study closely follow the key activities and outcomes in the FNP programme’s logic model [24], covering maternal health, child health and development, and maternal life course and are listed in Table 3.

The ability to report on outcomes will depend on several factors such as geographical and study cohort coverage, data quality (completeness and bias). As a result outcomes have been categorised into either short- or medium-term or descriptive. Short term outcomes (n=25) map well to the logic model, are known to have good data quality, and coverage across Scotland and our study cohort (thus maximising the number that can be formally analysed using statistical methods). These outcomes are likely to be associated with the pregnancy and birth period, and up to the child’s second birthday (e.g. child health outcomes). Medium-term outcomes (n=9) rely on data only measured in the period after the second birthday (e.g. school-based outcomes at age four-years of age onwards) and the population included in the analysis would be restricted as a result. These short- and medium-term outcomes will be formally analysed using statistical modelling and will compare between participants who did (Cases) and did not receive FNP provision (Controls).

Descriptive outcomes (n=20) are those where the direction of the FNP effect is either uncertain, outcomes are rare, or where the data are classed as experimental statistics (i.e. a type of official statistic that is undergoing development such as child attainment).

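### Cessation of breastfeeding is assigned to an ordinary proportional hazards model, but the listed source common to both groups appears to see feeding only at a few widely spaced reviews, so the event is probably interval-censored

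*Protocol article*

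**What the plan says.** Under Main analyses, the protocol article gives two examples of time-to-event outcomes and one model for both: "Time to event analyses (e.g. cessation of breastfeeding, time to subsequent birth) will be analysed using a proportional hazards regression model". Results are to be hazard ratios, and the stated check is "inspecting the log (-log(survival)) plot and Schoenfeld residuals". Interval censoring is not mentioned.

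Table 2, under Data sources and outcomes, lists one routine dataset in which preschool children are reviewed: "CHSP-Pre-School- Health Visitor first visit (~10 days); 6-8 week review; 27-30 month review; unscheduled review". Its coverage is national: "Contains data on the findings and outcome of the child health reviews for all children in Scotland". The FNP Scottish Information System (FNP SIS) also holds "clinical data recorded by FNs during their visits", but for FNP Clients only.

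The same section describes the horizon of short-term outcomes: "These outcomes are likely to be associated with the pregnancy and birth period, and up to the child’s second birthday". The article does not say which dataset or field supplies breastfeeding cessation, and the outcome list it refers to is not in the text at hand.

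**The concern.** The two examples differ in kind. A subsequent birth has a date, because SMR02 holds an episode record of each delivery. Nothing in Table 2 offers a comparable date for the end of breastfeeding. If a review records only whether the child is breastfed on that day, cessation is known to lie between two reviews and no closer.

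A Cox model given such data needs a date from somewhere, and the natural one is the review that first finds feeding stopped. Two things can then go wrong:

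- Women who have already stopped are counted as still at risk until their review, which pulls a real effect towards 1.
- If one group is reviewed slightly earlier, its events are recorded earlier, which looks like a difference in hazard.

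The planned diagnostics examine proportionality. They do not show that the event times are review dates.

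Every short- and medium-term outcome is given equal importance, with a confidence interval and p-value, and the results are to inform policy. A distorted ratio would therefore be read as evidence about FNP.

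**Working it through.** **No figure to reproduce.** The article gives no event count, effect size or power for this outcome ("no power calculation is necessary"). The check rests on the review schedule and stated assumptions.

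**Step 1: the gap in scheduled reviews.** 27 months is 27 × 365.25/12/7 = 117.4 weeks, and 117.4 − 8 = 109 weeks. 30 months is 130.4 weeks, and 130.4 − 6 = 124 weeks. So no review is scheduled for about 109 to 124 weeks after the 6-8 week review. Unscheduled reviews may fall in the gap. If cessation is a short-term outcome, the horizon is the second birthday (24 months). The 27-30 month review is then too late, and two scheduled looks remain.

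**Step 2: where cessations fall.** For an exponential duration with median m weeks (assumed), the share still feeding at day d is S(d) = 0.5^(d/7m). For m = 4, S(10) = 0.5^(10/28) = 0.78 and S(49) = 0.5^(49/28) = 0.30.

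| Median (weeks) | By day 10 | Day 10 to week 7 | After week 7 |
|---|---|---|---|
| 2 | 39% | 52% | 9% |
| 4 | 22% | 48% | 30% |
| 8 | 12% | 34% | 55% |
| 16 | 6% | 20% | 74% |

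**Step 3: Cox model with the event dated at the review.** Assumed:

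- 1000 Cases and 2000 Controls who start breastfeeding, in the 1:2 ratio of "around 3000 births in FNP cohorts between 2010 and 2015 and around 6000 in the Controls".
- Weibull cessation times, shape 0.8, median 21 days.
- First review at about day 11; 6-8 week review at mean day 49, SD 5 days unless stated.
- Breslow ties; women still feeding at the last review used are censored there.

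| True HR | Cases' 6-8 week review earlier by | Two early reviews | All three reviews |
|---|---|---|---|
| 1.00 | 0 days | 1.00-1.01 | 1.00 |
| 1.00 | 2 days | about 1.20 | about 1.02 |
| 1.00 | 2 days, SD 10 | about 1.09 | about 1.01 |
| 1.00 | 4 days | about 1.40 | about 1.04 |
| 0.80 | 0 days | about 0.84 | about 0.86 |

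With a 2-day difference and no true effect, about 98% of two-review tests are significant at SD 5 and about 53% at SD 10. At SD 2 the two-review ratio is about 1.49. A true 0.80 becomes about 1.00 in the two-review analysis with a 2-day difference at SD 5.

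**Step 4: other set-ups.**

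- Exponential durations with medians of 2 to 16 weeks, Efron ties, equal timing: a true 0.80 gives 0.81-0.87 with two reviews and 0.85-0.94 with three. A true 1.00 stays at 0.99-1.00.
- One extra unscheduled review at days 15-40 for 20% of women: the spurious ratio at a 2-day difference is still 1.17.

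**Step 5: does the remedy work?** In the exponential set-up, a grouped-time complementary log-log model on the two early reviews gives 0.79-0.81 for a true 0.80 under equal timing, and 1.00 for a true 1.00. If Cases are reviewed 7 days earlier and the model ignores it, a true 1.00 gives 0.87-0.91. Actual review dates must therefore enter as interval bounds.

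**The case against.** The strongest objection is that the premise is inferred. The article does not name the cessation field, and CHSP-Pre-School could hold a recalled stopping age. If so, recall error would remain but most of the point would go. This stands, and it limits the confidence.

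It can also be said that cessation is only an example in a condensed article, that a detailed SAP is promised before data access, and that all comparisons are labelled exploratory. The derivation of event dates is indeed SAP material. The model family, however, is stated here, and Schoenfeld residuals point to ordinary Cox regression. A discrete-time complementary log-log model is itself a proportional hazards model, so a generous reading of the sentence could admit the remedy.

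A reader might go further and infer that the hazard ratio will reflect review timing rather than when feeding stopped. The documents do not support that. They give no review ages by group. With equal timing the null is preserved and a real effect keeps its direction, with attenuation only. With the 27-30 month review included, the artefact at 2 days nearly disappears at SD 5 or 10. Nor does the article say that there is no information between the early and late reviews, since unscheduled reviews are listed, or that FNP SIS feeding dates will be used for Cases.

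**Conclusion.** The point holds in a limited form. The article assigns an ordinary proportional hazards model to an outcome that its listed common source appears to observe at two or three scheduled reviews plus unscheduled ones. Unless a stopping date or age is recorded, the data are interval-censored and the model fits them badly.

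The consequence that needs no assumption about timing differences is attenuation: a true 0.80 becomes about 0.84 (two early reviews) or 0.86 (all three). The larger consequence, a spurious ratio of about 1.1-1.2 for SD 10 to 5 days, needs a 2-day difference in mean age at the 6-8 week review and an analysis confined to the two early reviews. Such a difference is possible, since Controls come from periods without FNP enrolment and Cases receive a different service, but it is not shown.

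These sizes rest on assumed feeding duration, review spread and number of initiators, and on dating the event at the review. Confidence is moderate.

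**What to change.** Name the dataset and field that supply cessation. Unless a stopping date or age is recorded the same way in both groups, remove cessation of breastfeeding from the ordinary proportional hazards list and choose one of these:

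- Analyse feeding status at the 10-day and 6-8 week reviews as binary outcomes in the multilevel logistic model already planned, with the child's age in days at review as a covariate.
- If a single duration measure is wanted, fit an interval-censored or discrete-time complementary log-log model, with each woman's own review dates as interval bounds.

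Use the common source for both groups. Do not take feeding dates from FNP SIS for Cases only, since that would itself create unequal ascertainment. Report age at review by group. Keep the proportional hazards model for time to subsequent birth.

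The cost is a wording change and slightly more programming, with no new data. The downside is that one or two odds ratios replace a single hazard ratio if the binary route is taken.
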